### Outcome measures

#### Primary outcome measures

The primary outcome will be change in autonomous motivation to prevent T2DM. Autonomous motivation will be measured using the seven-item, validated Treatment Self-Regulation Questionnaire at baseline and 12-week follow-up [42].

#### Secondary outcome measures

The feasibility of recruitment will be determined by calculating the intervention uptake rate, defined as the number of participants recruited to the intervention divided by the total number of eligible participants. Because we may not be able to reach all eligible participants via telephone (e.g., disconnected phone line), we will also calculate the rate of intervention uptake among only those for whom we are able to contact. Reasons for non-participation in this study will be recorded.

Among JOOL-only and JOOL-plus participants, we will calculate rates of adherence to the JOOL Health application, defined as the number of app-usage days (defined as the number of days that users entered data into JOOL Health) divided by the total number of days during the intervention period. Among JOOL-plus participants, we will calculate rates of participant adherence to the Fitbit activity tracker and scale, defined as the number of total days that each of these devices were used divided by the total number of days during the intervention period.

Participant retention will be determined by calculating the completion rate for the 12-week survey.

The acceptability of the intervention will be determined through semi-structured interviews conducted via telephone. Following the intervention period, we will conduct semi-structured interviews with JOOL-only and JOOL-plus participants. For purposive sampling, we will interview individuals with differing levels of engagement with the intervention and change in autonomous motivation using cut-points for high and low levels of these determined following quantitative data analysis. We will conduct at least 20 interviews divided equally between JOOL-only and JOOL-plus participants; additional interviews will be conducted if we do not reach thematic saturation after 20 interviews [43, 44]. During the interviews, we will explore the following: reasons participants chose to engage in this study; participants’ experience with the JOOL Health application; and participants’ experiences with the Fitbit activity tracker and scale, if applicable. In this way, we will gain insight into the particular intervention characteristics (or combination of characteristics) that may have facilitated or hindered the participants’ ability to achieve the primary outcome. We will also solicit participants’ ideas regarding additional behavioral change supports and their recommendations on ways to improve the intervention.

We will evaluate change in HbA1c; baseline HbA1c will be abstracted from the electronic medical record and participants will be asked to have a follow-up HbA1c drawn after the 12-week intervention period. Additional exploratory outcomes will include change in the following self-reported measures: weight (kg) and/or BMI (kg/m^2^); change in overall level of motivation to prevent T2DM [34]; purpose in life [45, 46]; perceived competence to prevent type 2 diabetes [47]; social support [48]; eating behavior [49]; self-reported physical activity [50]; patient activation [51]; and willingness to participate in a Diabetes Prevention Program. We will collect these exploratory data at baseline and 12-weeks using survey instruments, which will be administered using RedCap, a secure web application [52]. At baseline, we will also collect sociodemographic characteristics including age, gender, race, ethnicity, education, and income. Among JOOL Health users, we will also evaluate changes in charted daily health behaviors (e.g., sleep, eating, physical activity) from baseline (first 2 weeks of the intervention) to 12-weeks (last 2 weeks of the intervention). Among participants in the JOOL-plus arm, we will also assess objective change in physical activity minutes and body weight as measured with the Fitbit activity tracker and scale from baseline (first 2 weeks of the intervention) to 12-weeks (last 2 weeks of the intervention). Because the Fitbit devices interface with the JOOL Health platform, Fitbit data will be stored within the JOOL Health application. At the end of the study period, the JOOL Health team will provide our study team with a comma-separated values (CSV) file containing raw data from the JOOL app and Fitbit devices.

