## Background

Within the USA, type 2 diabetes mellitus (T2DM) and its precursor, prediabetes, are growing public health concerns. Approximately 84 million adults have prediabetes [1], and it is estimated that one-third of the adult population will have T2DM by 2050 [2]. Diabetes Prevention Programs (DPPs) can promote modest weight loss [3–8] to help individuals with prediabetes avoid progression to T2DM [9–11], and these programs are available in communities throughout the USA [4, 12].

Despite nationwide availability of the DPP [4] and public health initiatives to identify and treat individuals with prediabetes [13, 14], rates of DPP engagement are extremely low [15]. Barriers to DPP participation include logistical factors (e.g., transportation, time, cost) [16] and behavioral factors (e.g., motivation, risk perception) [17–19]. Although web-based DPPs [20, 21] and growing insurance coverage for program participation [22–24] can reduce logistical barriers, these strategies alone have been inadequate to increase rates of DPP engagement. In September 2015, for example, a single University’s self-funded health insurers began to offer face-to-face and online DPP options to healthcare plan members (i.e., employees, retirees, and students of the University or their dependents) with prediabetes at no out-of-pocket-cost, yet only 6% of invitees enrolled in a DPP within 6 months. Prior work demonstrates an association between greater levels of autonomous motivation and increased engagement in healthy behaviors among this university’s employees with prediabetes [25]. This finding, in combination with low levels of program engagement, suggests that behavioral barriers may more strongly influence rates of DPP participation than logistical ones.

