### Study participants

Inclusion criteria are (1) non-participation in a formal DPP at least 6 months after invitation to participate by the University’s self-funded insurers, Premier Care or Grad Care; (2) prediabetes based on the American Diabetes Association criteria of hemoglobin A1c (HbA1c) 5.7 to 6.4%; (3) access to a personal smartphone; and (4) access to home wireless internet. We will exclude women who are pregnant or intend to become pregnant during the intervention period. All eligible study participants are employees, retirees, and students of this university or their dependents.

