### Data analysis

For all continuous outcomes, we will calculate changes from baseline to 12 weeks. For each continuous outcome, we will then conduct two sample *t* tests to determine whether the mean change for that outcome was statistically significantly different for each intervention arm relative to the comparison arm. For all categorical outcomes, we will use chi-square or Fisher’s exact tests to between-arm changes from baseline to 12 weeks. While we will be conducting multiple tests for statistical significance, we will not adjust our threshold for statistical significance (e.g., using a Bonferroni correction) for multiple comparisons so as to avoid making a type II error in this pilot study. We will conduct all analyses using Stata 14.

Semi-structured interviews will be audio recorded and subsequently transcribed verbatim. Interviews will then be imported into qualitative analysis software. Two investigators will independently read and code transcribed interviews. Interviews will then be coded jointly using consensus conferences. Interviews will be analyzed using directed content analysis [53].

Consistent with a mixed-methods sequential explanatory design [40], we will integrate (i.e., connect) the quantitative and qualitative findings in the final stage of data analysis. In this way, we will interpret our quantitative data in the context of qualitative participant experience.

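### HbA1c change is labelled a 12-week change, but its baseline comes from the medical record with no stated link to enrolment; adjusting for the record value is a cheap improvement

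*Protocol article*

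**What the plan says.** Under Secondary outcome measures, the protocol article takes the two HbA1c values from different sources: "baseline HbA1c will be abstracted from the electronic medical record and participants will be asked to have a follow-up HbA1c drawn". The follow-up sample is "drawn after the 12-week intervention period". The article does not tie the record value to enrolment.

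The survey outcomes in the same section are handled differently: "We will collect these exploratory data at baseline and 12-weeks using survey instruments". The app and Fitbit measures also have an anchored baseline, namely the first two weeks of the intervention.

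Under Study participants, eligibility requires "prediabetes based on the American Diabetes Association criteria of hemoglobin A1c (HbA1c) 5.7 to 6.4" per cent, and also "non-participation in a formal DPP at least 6 months after invitation to participate". The article does not say which HbA1c measurement establishes eligibility. The Background says that the DPP had been offered to plan members who already had prediabetes.

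Under Data analysis, one rule covers all of these outcomes: "For all continuous outcomes, we will calculate changes from baseline to 12 weeks". The method is "two sample *t* tests to determine whether the mean change for that outcome was statistically significantly different for each intervention arm", with the comparison group as the reference. No adjustment for the baseline value is mentioned.

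**The concern.** The Data analysis rule suits outcomes that are measured at study entry and again at 12 weeks. HbA1c is not described as being measured at entry. Its starting point is a value already in the record, so the interval to follow-up may be longer than 12 weeks and may differ between participants.

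Two things follow. First, if the record value is also the eligibility value, participants were selected because it fell within a narrow band. Follow-up values will then tend to move back towards the mean of the population they came from, whatever the intervention does. A mean change within one arm would contain that movement, plus any drift before enrolment. Second, subtracting a value that is only moderately correlated with follow-up adds noise to the between-arm comparison. The same value used as a covariate would not.

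The article says that the results will inform a larger trial. HbA1c is also the one clinical measure in all three arms that is not self-reported, so how its change is described and analysed is worth getting right.

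**Working it through.** **No plan figure to reproduce.** The article gives no effect, SD, correlation or power for HbA1c. Its sample size (29 per arm, enrolled as 35) concerns autonomous motivation only. The SDs, source means and correlations below are assumptions.

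**Step 1: is 12 weeks ensured?** The end of the interval is after the 12-week intervention. The start is the date of a record value, which the article does not state. The only earlier time it gives is the minimum of 6 months since the DPP invitation, and that dates an invitation, not a blood test. So the interval is not fixed at 12 weeks, and its actual length cannot be derived.

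**Step 2: precision when the baseline is the eligibility value.** Let X be the record value and Y the follow-up value, with equal SD *s* and correlation *r* in the source population. Let *t* be the SD of X after selection into the band. Selection on X leaves the regression of Y on X unchanged, so:

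- variance adjusted for X: s²(1 − r²)
- variance of Y − X: s²(1 − r²) + (1 − r)²t²
- ratio, adjusted to change = 1 / [1 + (t/s)²(1 − r)/(1 + r)]

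With s = 0.37 and t = 0.20, s² = 0.1369 and t² = 0.0400:

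| r | adjusted variance | change-score variance | ratio | reduction |
|---|---|---|---|---|
| 0.2 | 0.1314 | 0.1314 + 0.0256 = 0.1570 | 0.837 | 16% |
| 0.3 | 0.1246 | 0.1246 + 0.0196 = 0.1442 | 0.864 | 14% |
| 0.5 | 0.1027 | 0.1027 + 0.0100 = 0.1127 | 0.911 | 9% |
| 0.8 | 0.0493 | 0.0493 + 0.0016 = 0.0509 | 0.969 | 3% |

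A simulation with X restricted to 5.65 to 6.45 (the band before rounding), source mean 5.6 to 5.9% and source SD 0.35 to 0.40 agrees. Change-score variance was 1.14 to 1.15 times the adjusted variance at r = 0.3, and 1.03 times at r = 0.8.

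**Step 3: per-arm change with no treatment effect.** Under the same model, the expected change is −(1 − r) × (mean of selected X − source mean). In the simulation the selected mean lay about 0.30 points above a source mean of 5.6%, and about 0.11 above a source mean of 5.9%:

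- r = 0.3: −0.7 × 0.30 = −0.21, and −0.7 × 0.11 = about −0.07 points
- r = 0.8: −0.2 × 0.30 = −0.06, and −0.2 × 0.11 = about −0.02 points

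Every arm could therefore show an apparent fall of about 0.02 to 0.21 points from selection alone.

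**Step 4: validity of the planned test.** In 20,000 simulated trials with 29 per arm, a selected baseline (source mean 5.7%, SD 0.40, r = 0.8) and no effect, the two-sample t test on change rejected in 5.0% at a nominal 5%. The mean between-arm difference was 0.000.

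**The case against.** The strongest defence is that the planned comparison is valid. Randomisation spreads the age of the record value, drift and regression to the mean over all arms alike, and Step 4 confirms this. A t test on change scores is a legitimate analysis, and preferring ANCOVA is a matter of efficiency. For continuous outcomes the article plans only between-arm tests, so harm from a per-arm reading is conditional on someone making one. HbA1c is not primary and has no power claim. A look-back window may also stand in the full protocol, which an article need not repeat. All of this stands, and it limits the weight of the point. A short window would ease the timing problem but would leave the unadjusted change-score analysis as it is.

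Three stronger readings are tempting, and the article supports none of them:

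- **The interval is at least about nine months** (6 months plus 12 weeks). This assumes that the record value is the one behind the DPP invitation. A participant may have been retested since, and the article does not say.
- **The HbA1c comparison is biased.** It is not. Only a per-arm change read as a 12-week effect would mislead.
- **Adjustment would save 25 to 40% of the variance.** With equal SDs at both times the ratio is (1 + r)/2, which is 0.60 at r = 0.2 and 0.75 at r = 0.5. But equal SDs conflict with a baseline narrowed by eligibility while follow-up is not. If the record value were instead a later retest that is not range-restricted, the formula would apply, but a recent value should correlate more strongly. At r = 0.8 to 0.9 the saving is 10 to 5%.

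**Conclusion.** The point holds in a limited form. The Secondary outcome measures and Data analysis sections do not fit together for HbA1c: one takes baseline from the record without tying it to enrolment, and the other labels the difference a change over 12 weeks. The difference is not ensured to be a 12-week change; the article does not show that it is not one.

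The between-arm test keeps its nominal error rate and is unbiased. The loss is about 3 to 16% of variance, assuming that the record value is the eligibility value, with source SD 0.37, restricted SD 0.20 and correlation 0.2 to 0.8. A per-arm change could contain a spurious fall of roughly 0.02 to 0.21 points, for correlations of 0.3 to 0.8 and the source distributions assumed above. Its size, and even its direction, depend on where the source mean lies relative to the band. For a non-primary outcome in a pilot this is a minor improvement that costs little, and it does not invalidate the planned comparison.

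**What to change.** 1. Define baseline HbA1c as the most recent record value before randomisation, and abstract its test date.
2. Compare follow-up HbA1c between each intervention arm and the comparison arm by ANCOVA, with the record value as covariate. Time since that test may be added as a second covariate; its benefit has not been quantified, so it is optional.
3. Exempt HbA1c from the general rule on change from baseline to 12 weeks. Call the baseline a historical record value and report the actual interval to follow-up, for example its median and range by arm.
4. Do not interpret a per-arm HbA1c change as a 12-week effect.

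The cost is one extra abstracted date and a few words in the analysis text. No additional blood draw is needed. The one thing given up is a per-arm statement about 12-week HbA1c change, which the described data could not be relied on to support.

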### Sample size

Based on prior studies of autonomous motivation among University of Michigan employees [34], we anticipate that the baseline level of autonomous motivation to prevent T2DM among Premier Care or Grad Care members who decline DPP participation will be 5.7 (measured on a 1 to 7 scale with 1 being the lowest and 7 being the highest). During the 12-week intervention period, we anticipate that autonomous motivation will increase by 0.6 points in the JOOL-only arm and by 0.8 points in the JOOL-plus arm. Assuming a standard deviation of 1.0 for change in autonomous motivation in both arms, 29 participants in each arm will provide 80% power to detect these changes in autonomous motivation in the intervention arms compared to the comparison arm. Prior research demonstrates that a 0.5-point increase in autonomous motivation can lead to greater weight loss and increased physical activity compared to individuals who did not achieve this increase in autonomous motivation [36]. To account for the possibility that some participants may be lost to follow-up during our 12-week intervention, we have conservatively inflated our sample size by 20% to enroll 35 participants in each arm.

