## Discussion

Evidence-based Diabetes Prevention Programs are available in communities across the USA and can effectively promote weight loss among individuals with prediabetes [12]. However, the DPP alone may be insufficient to improve population health, as low rates of participation limit the program’s reach. Prior studies have described determinants of participation [17] and non-participation [16, 54, 55] in lifestyle-change programs, as well as barriers to adherence among those who initially engage in these programs [19]. However, it is unknown whether interventions to increase levels of autonomous motivation—a key driver of lifestyle change among individuals with prediabetes [25]—can promote healthy behaviors and greater rates of DPP engagement among individuals with prediabetes.

In this pilot study, we aim to test whether JOOL Health can increase autonomous motivation among individuals with prediabetes when used alone and also in conjunction with other mHealth tools. Because changes in individuals’ levels of autonomous motivation occur early along the path to behavioral change, we anticipate a large effect size from the intervention and will therefore have the power to detect between-group differences in this outcome in the context of a relatively small study (*N* = 105). This will serve as an important indicator that a larger study may lead to measurable changes in clinically relevant health outcomes such was body weight, physical activity, and DPP engagement. It is also possible that we will not detect changes in autonomous motivation. For this reason, we will conduct qualitative interviews with study participants so that we can interpret our quantitative findings in the context of individual-level participant experiences. For example, it is possible that some individuals may desire additional support (e.g., brief counseling, nutritional advice, explicit exercise goals) to augment the JOOL Health experience. Some individuals may want more tailored messaging from the JOOL Health application while others may find the daily charting to be burdensome. Understanding participants’ experiences will enable us to refine and strengthen our program. In this way, we will tailor our intervention to better meet the individual-level needs of this previously overlooked population with prediabetes who have not engaged in a formal DPP.

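### The stated 80% power with 29 per arm does not hold for JOOL-only under the planned t test: it is about 61% (two-sided 5%, no change in the comparison arm)

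*Protocol article*

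**What the plan says.** The Sample size section expects that "autonomous motivation will increase by 0.6 points in the JOOL-only arm and by 0.8 points in the JOOL-plus arm". It continues "Assuming a standard deviation of 1.0 for change in autonomous motivation in both arms" and concludes that "29 participants in each arm will provide 80% power to detect these changes in autonomous motivation", with the contrast given as "in the intervention arms compared to the comparison arm". Enrolment is then raised from 29 to 35 per arm to allow for loss to follow-up.

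The Data analysis section fixes the test. For each continuous outcome, which includes the primary one, two-sample t tests ask whether the mean change is "statistically significantly different for each intervention arm relative to the comparison arm". On multiplicity it says "we will not adjust our threshold for statistical significance". The article gives neither the significance level nor its sidedness, and it gives no expected change for the comparison arm.

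The Discussion relies on the power claim: it anticipates a large effect and says the study "will therefore have the power to detect between-group differences in this outcome".

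**The concern.** One sample size and one power figure are attached to two different effects. At a fixed number per arm and a fixed SD, a t test cannot have the same power for 0.6 as for 0.8. If 29 gives 80% for one of them, it gives something else for the other. The sentence could still stand as a minimum if 0.6 reached 80%, so the question is whether it does.

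JOOL-only against comparison is the direct test of the article's first hypothesis, that the app alone raises autonomous motivation more than written material. The Discussion treats detection of a difference as a signal for a larger trial. If the real power of that contrast is well below 80%, a non-significant JOOL-only result carries less evidence against the app than the article implies.

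**Working it through.** **Inputs from the article**

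- Mean gains: 0.6 (JOOL-only) and 0.8 (JOOL-plus), Sample size section.
- SD of change: 1.0, same section.
- Evaluable per arm: n = 29; enrolled per arm: 35.
- Test: two-sample t test of each intervention arm against comparison, Data analysis section.

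**Assumptions, not stated in the article**

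- Significance level 5%, two-sided (one-sided also tried).
- Zero change in the comparison arm, so the between-arm differences are δ = 0.6 and δ = 0.8.

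**Step 1: where 29 can come from.** For a three-arm one-way ANOVA F test, the noncentrality is λ = n × Σ(μᵢ − μ̄)² / SD².

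- Mean changes 0, 0.6, 0.8 give μ̄ = 1.4 / 3 = 0.4667.
- Σ(μᵢ − μ̄)² = 0.2178 + 0.0178 + 0.1111 = 0.3467.
- n = 28: λ = 28 × 0.3467 = 9.71, power 78.7%.
- n = 29: λ = 29 × 0.3467 = 10.05, power 80.3%.

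So 29 is the smallest n per arm that reaches 80% for the omnibus test. A pairwise t test for a difference of 0.75 also leads to 29, but the article gives no such difference.

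**Step 2: power of the planned t tests at n = 29.** The noncentrality is δ / SD × √(n/2), with 2n − 2 = 56 degrees of freedom. Here √(29/2) = 3.808, and the two-sided 5% critical value is 2.003.

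| Contrast with comparison | δ | Noncentrality | Power, two-sided 5% |
|---|---|---|---|
| JOOL-only | 0.6 | 0.6 × 3.808 = 2.285 | 61.2% |
| JOOL-plus | 0.8 | 0.8 × 3.808 = 3.046 | 84.9% |

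The normal approximation gives 62.7% and 86.1%, so the choice of formula does not matter.

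**Step 3: can another reading give 80% for JOOL-only?**

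- One-sided 5%, n = 29: 73.0%.
- Two-sided 5%, all 35 evaluable (noncentrality 0.6 × √(35/2) = 2.510): 69.7%.
- A within-arm one-sample test of 0.6 at n = 29: 87.7%. It needs only 24 for 80%, so it does not lead to 29, and it is not a comparison with the control arm.

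**Step 4: what would be needed.**

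- n per arm for 80% power, two-sided 5%: 45 for δ = 0.6 and 26 for δ = 0.8. Neither is 29.
- Smallest difference with 80% power at n = 29: 0.749, about 0.75.
- For JOOL-only to reach 80% at n = 29, either the SD of change would have to be about 0.6 / 0.749 = 0.80, or the comparison arm would have to fall by about 0.749 − 0.6 = 0.15. The article states neither.

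**The case against.** **The 29 has a coherent origin.** The omnibus ANOVA reproduces it exactly from the article's own effects and SD, with zero change in the comparison arm. A reader might infer instead that the figure is arbitrary or hides an unstated difference of 0.75; the match with the ANOVA means the article does not support that. The match does not rescue the sentence, though. The power statement is worded for the intervention arms against comparison, the Data analysis section plans pairwise t tests, and 80% power for an overall F test is not 80% power for each pair. That the ANOVA was actually used remains a conjecture.

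**The level, its sidedness and the comparison-arm change are not stated.** This stands, and it is why 61% must be given with its conditions. A fuller document may state them, so their absence from an article is not itself the fault. At n = 29, neither sidedness of a 5% test brings JOOL-only to 80%. The most generous combination, one-sided 5% with all 35 enrolled participants evaluable, comes to 79.96%, but the claim is made for 29. A reader might also infer that the comparison arm will improve, since it receives prevention information, and that true power is lower still. The article gives no figure for such a change, so the finding does not rest on it.

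**It is a pilot.** The first aim is framed as estimation, feasibility and acceptability form the second, and the Discussion openly allows that no change may be detected and plans interviews to interpret that. JOOL-plus is adequately powered, and simulation under the same assumptions gives about 89% power for at least one of the two tests. All of this limits the consequence. It does not make the sentence correct: the article chose to state a power and relies on it in the Discussion.

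**The 0.5-point figure.** A reader might set the detectable difference of 0.75 against the 0.5-point increase mentioned in the Sample size section and conclude that the trial cannot detect what matters. That 0.5 is an increase within individuals, not a target difference between arms, and the article claims no power for it.

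**Conclusion.** The power statement is wrong as written for one of the two primary comparisons. Under the planned two-sample t test with 29 per arm, SD 1.0, two-sided 5% and zero change in the comparison arm, power is about 61% for JOOL-only and about 85% for JOOL-plus. On the article's own effect size, a true JOOL-only benefit would be missed about 100 − 61 = 39% of the time, roughly twice the 20% that the text implies.

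The likely explanation is a sample size computed for one test and an analysis planned with another. A reader might infer that the trial as a whole is underpowered or must grow. The article does not support that: the JOOL-plus contrast exceeds 80%, and the aims of a pilot do not require every contrast to reach it. The error lies in what is claimed, not in the enrolment target or the choice of analysis.

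**What to change.** Keep 35 per arm and the planned t tests. In the Sample size section, replace the single 80% with power for each contrast: with 29 evaluable per arm, about 85% for JOOL-plus against comparison (0.8) and about 61% for JOOL-only against comparison (0.6), with a detectable between-arm difference of about 0.75 at 80% power. State the significance level and its sidedness, and that no change is assumed in the comparison arm. If the 29 did come from an omnibus ANOVA, say so and note that it is not the planned analysis. If a different level or sidedness was intended, recompute the figures for it.

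Qualify the Discussion sentence on power so that it separates the two contrasts and a non-significant JOOL-only result is not read as coming from an 80%-powered comparison.

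The cost is wording only, with no added participants and no change of analysis. The downside is that the stated power for one arm becomes less favourable.
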